
## Statistical methods

### Statistical methods for primary and secondary outcomes

We will employ a zero-shot prompting approach with OpenAI's recently released GPT-OSS (Generative Pretrained Transformer—Open Source Software) series models, which are available under the permissive Apache 2.0 license and have demonstrated strong performance on reasoning tasks relevant to clinical assessment. We have selected these models for several methodological and practical reasons:

First, their open-weight nature ensures full transparency and reproducibility of our analyses. Second, their mixture-of-experts architecture enables efficient deployment on clinical infrastructure with limited computational resources. Third, their documented performance on complex reasoning tasks, including healthcare-related queries, makes them well-suited for psychiatric assessment applications.

Our primary analytical comparison will involve two model sizes from the GPT-OSS family: GPT-OSS-120B (116.8 billion total parameters with 5.1 billion active parameters per token) and GPT-OSS-20B (20.9 billion total parameters with 3.6 billion active parameters per token) (58). This comparison directly addresses a critical question for clinical deployment: whether larger, more capable models provide sufficient performance advantages to justify their greater computational demands, or whether smaller, more efficient models can achieve comparable diagnostic accuracy. The GPT-OSS-120B model has been shown to achieve near-parity with state-of-the-art reasoning models on standard benchmarks while running efficiently on a single 80GB GPU, whereas GPT-OSS-20B delivers comparable performance to advanced compact models while requiring only 16GB of memory, making it feasible for deployment on standard clinical workstations or even edge devices.

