For each model size, we will systematically evaluate two distinct inference configurations defined by the temperature hyperparameter, which controls the randomness of model outputs. We will test a conservative configuration (temperature = 0.1) designed to prioritize consistency and clinical reliability by producing more deterministic responses, and a rather liberal configuration (temperature = 0.8). In the NLP literature the effects of temperature are well represented but systematic clinical applications have yet to be done to our knowledge. Accuracy in multiple choice question answering tasks show high consistency in temperature ranging between 0 and 1, but an expansion to other problem types is recommended (59). This strategic selection of hyperparameters reflects the clinical tension between reproducibility critical for diagnostic applications where consistency across assessments is paramount and the risk of highly inconsistent outcomes that could potentially lead to incorrect diagnoses and treatment recommendations. In addition, we apply top-p (nucleus) sampling with a cumulative probability threshold of 0.9 to each analysis. This setting restricts sampling to the smallest set of tokens whose cumulative probability mass is at least 0.9, balancing output diversity with coherence.

This yields a 2 × 2 factorial design with four experimental conditions: 1. GPT-OSS-120B with temperature 0.1, 2. GPT-OSS-120B with temperature 0.8, 3. GPT-OSS-20B with temperature 0.1, and 4. GPT-OSS-20B with temperature 0.8. We will evaluate each condition's performance on primary outcomes including general diagnostic classification accuracy and suicidality detection, severity score prediction (correlation with standardized clinical measures), and clinical utility metrics such as sensitivity, specificity, and positive/negative predictive values. All model versions, hyperparameters, and inference code will be fully documented and made available to ensure complete reproducibility.

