Tier 1: Unimodal Baseline Analysis. We will analyze each modality independently to establish baseline predictive performance before considering fusion. For the text modality, we will conduct two-way mixed-effects logistic regression with outcomes (diagnostic classification or severity degree) regressed on the fixed effects of model size and temperature, with random intercepts for participant and session. Effect sizes will be reported as odds ratios with 95% confidence intervals. For the acoustic modality, we will conduct mixed-effects linear regression using a reduced set of the most clinically relevant acoustic features selected *a priori* based on prior literature associations with depression and suicidality, including pitch variability, energy measures, MFCC and jitter as predictors of continuously scored clinical outcomes (e.g., severity scores from standardized rating scales) (60, 61).Tier 2: Factorial Interaction Analysis for 2 × 2 Design. For text-based predictions, we will formally test the 2 × 2 factorial design using mixed-effects ANOVA to partition variance according to main effects (model size, temperature) and their interaction. Specifically, we will model primary outcome (e.g., predicted depression severity) as a function of fixed effects for model size (GPT-OSS-120B vs. 20B), temperature (0.1 vs. 0.8), and their interaction (Model Size × Temperature), with random intercepts for participants and sessions to account for the hierarchical data structure. This approach allows us to determine whether inference strategy recommendations (conservative vs. liberal temperature) can be applied consistently across model sizes, or whether optimization differs by model choice. If a significant Model Size × Temperature interaction emerges, it would suggest that clinical deployment requires model-specific tuning. Conversely, absence of interaction would support unified recommendations applicable regardless of computational constraints. We will report partial eta-squared (*η*²p) effect sizes with 95% confidence intervals for each factorial term.Tier 3: Multimodal fusion and Late-Fusion Integration. To evaluate how textual and acoustic information combine for clinical prediction, we will employ a structured late-fusion approach. For each of the four 2 × 2 factorial conditions, we will generate separate predictions from the GPT-OSS models (text modality) and from a logistic regression model trained on acoustic features (acoustic modality). We will then integrate these predictions through weighted averaging, with weights determined via cross-validation (80% training, 20% held-out validation) on a stratified subset of sessions. This approach maintains interpretability—each modality's contribution can be quantified—and avoids the architectural complexity that would introduce uncontrolled hyperparameter flexibility incompatible with pre-registration.We will quantify multimodal benefit by comparing fusion performance (AUC, sensitivity/specificity at clinically relevant decision thresholds) against the best unimodal baseline. If fusion provides incremental improvement beyond single modalities, we will use mixed-effects logistic regression with interaction terms to test whether the fusion benefit depends on model size or temperature setting. This tests the hypothesis that acoustic information provides complementary information that enhances text-based predictions uniformly, or whether certain model configurations better leverage multimodal information.

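### The 120B versus 20B comparison asks how much better the larger model is, but the only interval-bearing effect measures named for it are a conditional odds ratio and a partial eta-squared; no paired absolute difference with an interval is stated

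*Protocol article*

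**What the plan says.** All of this stands in the protocol article under Statistical methods for primary and secondary outcomes.

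- **The question.** The comparison of GPT-OSS-120B with GPT-OSS-20B is called the primary analytical comparison. It is to settle "whether larger, more capable models provide sufficient performance advantages to justify their greater computational demands". The alternative answer that the article names is that "smaller, more efficient models can achieve comparable diagnostic accuracy".
- **Per-condition measures.** Each of the four size-by-temperature conditions is evaluated on "performance on primary outcomes including general diagnostic classification accuracy and suicidality detection, severity score prediction", and on "clinical utility metrics such as sensitivity, specificity, and positive/negative predictive values".
- **Tier 1, text modality.** A mixed-effects logistic regression has "fixed effects of model size and temperature, with random intercepts for participant and session". On how its results are to be expressed, the article states: "Effect sizes will be reported as odds ratios with 95% confidence intervals".
- **Tier 2.** A mixed-effects ANOVA tests size, temperature and their interaction, with predicted depression severity as the example outcome. "We will report partial eta-squared" is followed by a commitment to "effect sizes with 95% confidence intervals for each factorial term".
- **Tier 3.** AUC, sensitivity and specificity appear again, but to compare fusion with the best single modality, not 120B with 20B.

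The article then tests the size effect at a two-tailed 0.05 level and says that comparisons between specific cells will be pre-specified and corrected for multiplicity. It does not name their scale or an interval.

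**The concern.** Whether an advantage is large enough to pay for is a question of amount, in units that can be set against computing cost: percentage points of accuracy, missed or falsely flagged cases, score points of error. The two measures that carry intervals are not in such units.

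All four configurations read the same sessions, so correct and incorrect results will tend to be correlated within a session. In a random-intercept logistic model the odds ratio is conditional on the participant and session intercepts. For a fixed gain in accuracy it moves away from 1 as the intercept variance grows. A reader who has the odds ratio and its interval, but not the intercept SD and the baseline accuracy, cannot turn them into percentage points.

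Partial eta-squared depends on the residual variance as much as on the shift. With predicted severity as the outcome, it also measures whether the two models' predictions differ, not which model is nearer the gold standard.

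At stake is the deployment recommendation. Two per-condition accuracies give a point difference, but no valid interval for it, because the interval must use the pairing within sessions and the clustering of sessions within participants.

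**Working it through.** **The plan's own figures.** The article gives no figure for the model-size contrast. Its one design figure, 162, concerns model versus gold standard. It reproduces (exact two-sided binomial test, 0.61 against 0.50: critical values 68 and 94, alpha 0.0492, power 0.8047) but does not bear on this point. Below, 162 serves only as a number of sessions.

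**Inputs.** From the article: expected accuracy 0.892, 162 sessions, four readings per session, random intercepts. Assumed, because the article gives none: intercept SD *s* from 0 to 5 (one combined normal intercept), the accuracies of the two models, and the residual SDs. The logistic outcome is taken to be correct versus incorrect, which is the reading most favourable to the plan.

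**Step 1. One accuracy gain, many odds ratios.** Marginal accuracy is p = ∫ expit(b + s·z) φ(z) dz. Solve for b at p = 0.80 (20B) and p = 0.85 (120B). The conditional odds ratio is exp(b₁₂₀ − b₂₀).

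| s | b₂₀ | b₁₂₀ | Odds ratio |
|---|---|---|---|
| 0 | 1.386 | 1.735 | 1.42 |
| 1 | 1.650 | 2.048 | 1.49 |
| 2 | 2.228 | 2.752 | 1.69 |
| 3 | 2.929 | 3.611 | 1.98 |
| 4 | 3.685 | 4.540 | 2.35 |
| 5 | 4.470 | 5.506 | 2.82 |

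The first row by hand: (0.85/0.15)/(0.80/0.20) = 5.667/4 = 1.42. The gain is 5 percentage points in every row.

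**Step 2. One odds ratio, many accuracy gains.** Fix the conditional odds ratio at 2.0 and read back the gain in percentage points:

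| 20B accuracy | s = 0 | s = 3 |
|---|---|---|
| 0.70 | 12.4 | 6.5 |
| 0.80 | 8.9 | 5.1 |
| 0.892 | 5.1 | 3.2 |
| 0.95 | 2.4 | 1.7 |

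The same reported effect covers gains from 1.7 to 12.4 points.

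**Step 3. Partial eta-squared under the planned model.** Take N = 162 sessions, four readings each and random intercepts only (one session per participant, for simplicity). For a mean size difference d and residual SD σ:

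- SS = 4N(d/2)² = N·d²
- SSE = 3(N − 1)σ² = 483σ²
- partial eta-squared = SS/(SS + SSE)

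For d = 1 score point:

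- σ = 1: 162/(162 + 483) = 0.251
- σ = 2: 162/(162 + 1,932) = 0.077
- σ = 4: 162/(162 + 7,728) = 0.021
- σ = 8: 162/(162 + 30,912) = 0.005

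The value can be large or small for one and the same shift.

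**Step 4. A shift in predictions is not a gain in accuracy.** Suppose 120B predicts on average 1 point too high and 20B 1 point too low, with equal spread. Neither model is nearer the truth. Yet d = 2, and at σ = 2 partial eta-squared is 648/(648 + 1,932) = 0.251.

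**Step 5. Why the interval needs the pairing.** Take accuracies of 0.80 and 0.85 in 162 sessions, one reading per model.

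- Ignoring pairing: variance (0.80·0.20 + 0.85·0.15)/162 = 0.2875/162. Half-width 1.96·√0.001775 = 8.3 points.
- With pairing at s = 3: the probability that both are correct is 0.749, so the discordant probabilities are 0.101 and 0.051. Variance (0.101 + 0.051 − 0.05²)/162 = 0.1495/162. Half-width 1.96·√0.000923 = 6.0 points.

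The two intervals run from about −3.3 to 13.3 and from about −1.0 to 11.0 points, both before clustering by participant. A bare 5-point difference does not show whether 120B is better, comparable or undetermined.

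**The case against.** The strongest reply is that the plan already provides absolute measures. It commits to accuracy, sensitivity, specificity and predictive values for each condition on the same sessions, so the gap between models is one subtraction. This stands. A reader might infer that the size effect is reported only as an odds ratio and eta-squared, or that the plan cannot answer its deployment question. The per-condition commitment contradicts the first, and the second goes further than the text supports.

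A second reply is that the planned measures are standard. The random-intercept logistic model does account for within-session correlation, and a conditional odds ratio is a legitimate quantity. That is also true. The point is not that they are wrong, but that on their own they do not give the amount the question asks for.

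Third, the intercept SDs are assumed, and at modest values the odds ratio moves little: 1.49 at SD 1 and 1.69 at SD 2, against 1.42 at SD 0. The full range is therefore shown. A reader might likewise infer that partial eta-squared makes trivial shifts look sizeable. Step 3 shows that it can go either way with the residual SD, so no general claim of overstatement is supported.

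Finally, an article may leave interval methods to the full protocol or analysis plan. That excuses silence on bootstrap details and on a margin for calling the models comparable, and neither is raised here. It does not cover the mismatch itself: the article positively names the effect measures for the size factor, and presents its framework as closed to later flexibility.

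**Conclusion.** The point holds in a limited form. The article asks an amount question about 120B versus 20B and plans the per-condition values from which a point difference follows. The only interval-bearing measures it names for the size effect, however, do not express that amount. For one gain from 80% to 85% the odds ratio runs from 1.42 to 2.82 over assumed intercept SDs of 0 to 5. An odds ratio of 2.0 corresponds to anything from 1.7 to 12.4 points over assumed 20B accuracies of 0.70 to 0.95 and SDs of 0 to 3. Partial eta-squared has no unit and, on the article's example outcome, does not measure accuracy.

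These sizes are illustrations, since the article gives no intercept SD, residual SD or expected model-size effect. That the odds ratio grows with the intercept variance for a fixed gain in accuracy does not depend on the values chosen. This is a worthwhile, cheap improvement to what is reported; it does not invalidate the planned models or tests.

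**What to change.** For the 120B versus 20B comparison, name as the main reported effect:

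- the paired difference (120B minus 20B, same sessions) in accuracy, sensitivity and specificity, in percentage points;
- the paired difference in mean absolute error of the predicted score against the gold standard, in score points.

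Give each a 95% interval from a bootstrap that resamples participants and carries along all of a participant's sessions and all four model readings. This respects both the pairing and the up to five sessions per participant. Keep the odds ratios and partial eta-squared as supplementary results.

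The cost is a short addition to the statistical methods and a little more analysis code. No new data, recordings or model runs are needed.

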With our study, we aim to fill this gap by applying recent advances in NLP and multimodal methods. Our goal is to help identify non-explicit content language patterns in clinical patients, which can serve as prognostic markers specifically for the German language. Thus, our primary aim is to assess the suicide risk in patients with depression, bipolar disorder, and psychotic disorders, such as schizophrenia, schizoaffective disorder and acute polymorphic psychotic disorder (according to ICD-10), as well as the psychopathological development (Clinical Global Impression, CGI). As a secondary outcome we want to assess the overall psychopathological condition of the patients. This includes standardized and validated questionnaires comprising the clinician's impression of the patients general psychosocial functioning (Global Assessment of Functioning, GAF), suicidal symptoms (Depressive Symptom Index—Suicidality Subscale, DSI-SS) and suicidality (Suicidal Scale of the Mini-International) as well as electronic health records (EHR) of the patient's psychopharmacological medication. Generally, the standardized text of the patient's EHR will be accessible for the text-based analysis. These will be supplemented by the standardized assessment through a clinician, which will be used as the gold standard for comparison with the AI analysis.

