### Eligibility criteria

We will include patients with ICD-10 diagnoses F20.x, F23, F25, F30-33, aged between 18 and 65 years, who are legally competent, without any issues in voice production, and have a German speaking proficiency of at least B2 (lower level in German would contain too little information content of linguistic utterances). Additionally, psychotherapists employed at the University Hospital Frankfurt will be included for the therapeutic conversations.

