### Participant timeline

In-patients and out-patients will regularly be screened for participation eligibility. If the eligibility criteria are met and in consultation with their treating clinicians, patients will be informed about their study and will have at least one day to consider participation and sign the informed consent. The same procedure applies for clinicians who participate in the study, while they only must consent once for the recording of therapy sessions with several patients who gave informed consent. From the time point on where patients agreed to participate, up to five of their regularly held therapy sessions will be recorded. After the therapy session, patients and therapists will fill out questionnaires about the psychopathology of the patient (approx. 5 min. for each). They are asked to fill out the questionnaire on the same day the therapy session took place. Table 1 summarizes the procedure and when the respective questionnaires are used.

**Table 1 T1:** Content for the schedule of enrollment and participation.

TIMEPOINT	Enrollment	Informed Consent	Recording and Questionnaires				
	*−t2*	*−t1*	*t1*	*t2*	*t3*	*t4*	*t5*
	Ongoing	After confirmation by clinician	At least 1 week between each participation				
			Up to five therapy sessions can be recorded per participant				
			Questionnaires have to be filled out the same day as the recording				
*Study admission*							
Eligibility screen	X	X					
Consultation with the treating clinician	X						
Informed consent		X					
*Recording of therapy session*			X	X	X	X	X
*Patient reported outcomes (PRO)*							
*Beck’s Depression Inventory (BDI-II)*			X	X	X	X	X
*DSI-SS-Scale*			X	X	X	X	X
MINI C Suicidality Scale			X				
*Demographics, Diagnoses and Concomitant Medication*			X				
*Therapist Ratings*							
*Global Assessment of Functioning (GAF)*			X	X	X	X	X
*Clinical Global Impression (CGI)*			X	X	X	X	X
*Brief Psychiatric Rating Scale (BPRS)*			X	X	X	X	X

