Concurrent with text-based analysis using GPT-OSS models, we will extract acoustic features from therapy session recordings using openSMILE (version 3.0) (56) with the eGeMAPSv02 feature set (60), which includes validated markers known to associate with psychiatric conditions. The eGeMAPSv02 feature set comprises 88 acoustic features encompassing spectral (Mel-frequency cepstral coefficients), glottal (fundamental frequency, jitter, shimmer), and prosodic characteristics (energy, speech rate, voice quality measures such as harmonics-to-noise ratio). These features will be extracted at the frame-level (10-millisecond intervals) and subsequently aggregated using statistical functions (mean, standard deviation, minimum, maximum, percentiles) to produce session-level representations comparable to clinical assessment timeframes.

Our overarching analytical strategy employs a three-tier statistical framework designed to characterize how textual, acoustic, and combined modalities contribute to clinical prediction:

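### The acoustic regression names only voice features, chosen from depression and suicidality literature, in a trans-diagnostic sample, so pooled slopes may be diluted or may partly reflect diagnosis

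*Protocol article*

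**What the plan says.** The Protocol article, under Statistical methods for primary and secondary outcomes, Tier 1, states for the acoustic modality: "we will conduct mixed-effects linear regression using a reduced set of the most clinically relevant acoustic features". The selection is made in advance and is "based on prior literature associations with depression and suicidality". The predictors and outcome are given as "including pitch variability, energy measures, MFCC and jitter as predictors of continuously scored clinical outcomes", with severity scores from rating scales as the example.

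Eligibility criteria: "We will include patients with ICD-10 diagnoses F20.x, F23, F25, F30-33". Objectives describes the corpus as trans-diagnostic, and the primary aim is to "assess the suicide risk in patients with depression, bipolar disorder, and psychotic disorders".

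The three tiers and the paragraph on assumption checks name no diagnosis main effect, no feature-by-diagnosis interaction and no fit by diagnosis for the acoustic model. Diagnosis is available: the schedule in Participant timeline (Table 1) has a row "Demographics, Diagnoses and Concomitant Medication" marked at t1.

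Tier 1 has a stated purpose: "We will analyze each modality independently to establish baseline predictive performance before considering fusion". The Statistical methods section closes by saying that the approach follows pre-registration principles and leaves no room for changing methods afterwards.

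**The concern.** The basis for choosing the features is narrower than the population. Features picked for depression and suicidality are used to predict general severity in people who may instead have a psychotic or bipolar disorder. With acoustic predictors only, each feature has one slope for everybody. Two things can follow:

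- **Dilution.** If a feature tracks severity in one diagnosis and not, or differently, in another, the pooled slope is a weighted average and a real association can be missed.
- **Confounding by diagnosis.** If diagnoses differ on average in both the feature and the score, a pooled slope can appear although the feature tracks severity within no diagnosis.

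This matters because the voice results will not be used only for prediction. Objectives looks for patterns that could serve as prognostic markers, and Data management plans correlations of audio features with symptoms and severity scores. Diagnostic classification is a separate primary outcome, so a severity coefficient that merely separates diagnoses answers a different question.

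**Working it through.** **Plan's own figure.** The article gives none for the acoustic regression. The sample size of 162 belongs to a test of accuracy and does not bear on this point.

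**Inputs from the article.** Diagnoses enrolled; acoustic predictors only; diagnosis recorded at t1; up to five sessions per patient; 162 sessions required and 200 planned.

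**Assumed inputs.** Diagnosis shares, slopes, group mean differences, and an intraclass correlation of 0.5 for both voice and severity. Features are standardised within diagnosis, with equal variance. The order below is depression / mania / psychosis. All values are illustrative.

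**Step 1, formula.** With shares w, within-group slopes b, and group means of feature and score expressed as deviations dx and dy from the overall mean:

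pooled slope = [Σ w·b + Σ w·dx·dy] / [1 + Σ w·dx²]

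**Step 2, dilution (no mean differences).** The formula reduces to Σ w·b.

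| Shares | slopes -0.4 / +0.4 / 0 | slopes -0.4 / 0 / 0 |
|---|---|---|
| equal thirds | 0.00 | -0.13 |
| 50/25/25 | -0.10 | -0.20 |
| 60/10/30 | -0.20 | -0.24 |
| 80/5/15 | -0.30 | -0.32 |

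Full cancelling needs opposite slopes in groups of equal size. Otherwise the slope shrinks, and in a mainly depressed sample it shrinks little.

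**Step 3, power cost if sessions were independent.** Fisher z: power ≈ Φ(atanh|r|·√(n - 3) - 1.96). Take shares of 50% depression, 20% mania and 30% psychosis.

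- Slopes -0.4 / +0.4 / 0: 0.5(-0.4) + 0.2(0.4) = -0.12. At n = 162, 0.1206 × 12.61 = 1.52, so power is 33%. The depressive half alone (n = 81, r = 0.4) has 0.4236 × 8.83 = 3.74, so power is 96%.
- Slopes -0.4 / 0 / 0: -0.20, power 72%.
- Slopes -0.4 / 0 / -0.2: 0.5(-0.4) + 0.3(-0.2) = -0.26, power 92%.

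Repeated sessions from one patient carry less information than these figures suppose.

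**Step 4, confounding (zero slope in every diagnosis).** Let depression and mania be shifted by s in opposite directions on the feature, with the score shifted the other way. At 50/25/25 and s = 0.8, the mean shift is -0.5(0.8) + 0.25(0.8) = -0.2. Then Σ w·dx² = 0.5(0.36) + 0.25(1.00) + 0.25(0.04) = 0.44, and the slope is -0.44/1.44 = -0.31. At s = 0.5 it is -0.15 and at s = 0.3 it is -0.06. Across the four mixes in the table the range for s = 0.3 to 0.8 is -0.03 to -0.31.

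**Step 5, with a participant random intercept.** The same null case at 50/25/25 was simulated as a random-intercept linear model, 200 runs per scenario.

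| Design | shift | mean slope, no diagnosis term | false positives, no diagnosis term | false positives, with diagnosis term |
|---|---|---|---|---|
| 40 patients × 5 | 0.5 SD | -0.04 | 0.07 | not run |
| 40 patients × 5 | 0.8 SD | -0.09 | 0.25 | 0.06 |
| 81 patients × 2 | 0.5 SD | -0.10 | 0.27 | not run |
| 81 patients × 2 | 0.8 SD | -0.20 | 0.68 | 0.045 |

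The Monte Carlo standard error is at most √(0.25/200) = 0.035. The random intercept reduces the spurious slope (from -0.31 to between -0.09 and -0.20 at 0.8 SD) but does not remove it. The diagnosis term brings it to about zero (0.01 and -0.01).

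**The case against.** Four arguments on the other side carry weight.

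1. **Silence is not exclusion.** The article never says that diagnosis is left out, its feature list is not exhaustive, and covariates are often left to a fuller document. This stands, so the point is limited to the model as written. It is weakened because the section spells out fixed effects, random intercepts and a multiplicity rule for the text models, and then presents the whole as closing off later choices.
2. **Tier 1 is about prediction.** Voice differences between diagnoses are legitimate predictive signal, and a pooled slope is not invalid for that purpose. This stands, and the pooled model should stay.
3. **Suicidality is relevant in every included diagnosis**, and the parent feature set is described as one "which includes validated markers known to associate with psychiatric conditions". This stands. The mismatch is therefore strongest for the general severity scores and weaker for suicidality.
4. **The mechanism is assumed.** A reader might infer that a feature such as vocal energy falls with severity in depression and rises in mania, so that effects cancel and any association found is really diagnosis. The article gives no direction of association by diagnosis and no diagnosis mix, so it supports neither statement as fact. Dilution and confounding are possible, not shown.

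Two tempting remedies also fail. Making the depressive group the main test would give up the trans-diagnostic aim. Adding diagnosis to the acoustic predictor in Tier 3 would feed in the answer where diagnosis is the outcome, and elsewhere would credit voice with information that is not voice.

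**Conclusion.** The point holds in a limited form. The article chooses features for depression and suicidality, applies them to a wider sample, and names no diagnosis effect in the severity model. Slopes may be diluted, or may partly reflect diagnosis differences in voice and severity.

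The size is open. Under the assumed inputs, dilution ranges from slight (-0.4 to -0.32) to complete (0.00), and the false-positive rate for a feature with no within-diagnosis effect ranges from 0.07 to 0.68. Where in those ranges the study falls depends on the diagnosis mix, the slopes, the group differences and the sessions per patient. The article fixes none of these beyond a maximum of five sessions.

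The stronger reading, that the pooled model cannot answer the question for any patient group, is not supported: it remains a valid predictive baseline. What is not secured is the step from a pooled coefficient to a voice marker of severity. This merits a change of wording before analysis. It does not undermine the design.

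**What to change.** - Keep the pooled acoustic-only model as the unimodal predictive baseline.
- Pre-specify beside it the same model with diagnosis group as a main effect, using the groups named in the primary aim (depression, bipolar disorder, psychotic disorders) and the diagnosis recorded at t1.
- Report feature slopes by diagnosis with confidence intervals, as description and not as separate confirmatory tests.
- State that a feature will be called a severity marker only if its association holds after adjustment for diagnosis, and say what counts as holding (for example, an adjusted interval that excludes zero).
- Leave diagnosis out of the Tier 3 acoustic predictor, and do not restrict the main test to the depressive group.
- If a fuller analysis document already contains the diagnosis term, one sentence saying so is enough.

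**Cost.** No new data. Three groups add two parameters for the main effect and two per feature for the slopes. One feature from each of the four named families would give 2 + 2 × 4 = 10, and more if a family contributes several measures. Intervals in the smaller groups will be wide: a 25% group is 10 patients in a 40-patient sample and about 20 in one of 81. That is why the slopes by diagnosis should be descriptive. A bipolar group also mixes manic and depressive episodes, so the diagnosis term will not capture every difference.
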